### Analyses

On the basis of an intention-to-treat analysis, differences between the intervention groups and usual care group are calculated with 95% confidence intervals. In addition per protocol analyses will be performed. The subgroups SU and non-SU will be analysed separately for all outcome measures. In case there is no effect modification by treatment the data of both subgroups will be pooled. If there are any relevant differences in baseline measurements between the 3 arms, we will adjust the outcomes for these factors (i.e. age, gender, ethnicity, status of depression, diabetes duration, marital status, level of education). Linear and logistic regression will be used to determine the effect of the intervention on each of the outcome measurements. The effect of the intervention will be estimated for sub-groups defined by duration of diabetes, socio-economic status, perceived social support and perceived severity of diabetes, glycaemic control and self-monitoring frequency in order to gain a better understanding as to who benefits most from the intervention. Analyses of moderators and mediators will be performed for the process-evaluation.

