### Sample size

The proposed trial is designed to detect a clinically relevant change of self-monitoring of glucose on diabetes specific emotional distress and self-efficacy. No consensus exists about minimal important differences (MID) of diabetes specific distress measured with the PAID and self-efficacy measured with the CIDS. Therefore we set the MID at half a standard deviation [35]. In diabetes patients the standard deviation (SD) of PAID (scores transformed to 0–100) was 20 points [25]. Using a bonferroni correction based on two primary hypotheses with α 0.025 and β 0.15, a sample size of 86 per group is needed to find a difference of 10 points (0.5 SD). Information on the SD of the CIDS is not yet available for T2DM patients. For type 1 diabetes patients the SD of CIDS (scores transformed to 0–100) was 12 points [26]. To detect a decrease of 6 points (0.5 SD), while correcting according to bonferroni based on two primary hypotheses with α 0.025 and β 0.15 a sample size of 86 per group is needed. Taking into account different effects in different treatment groups (SU or non-SU) pre-stratification by treatment will double the sample size. Assuming a 15% drop-out rate, a total of 600 T2DM patients with HbA1c ≥ 7.0% are needed in the study. In addition, with a total of 600 patients it is expected to have sufficient power to detect a clinically relevant decrease of 0.5% in HbA1c.

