## Discussion

This article presents a detailed description of a RCT, designed to explore the effectiveness of SMBG and SMUG on diabetes specific emotional distress and self-efficacy in non-insulin dependent T2DM patients. The proposed trial is sufficiently powered and, to the best of our knowledge, the first to allow for conclusions on the effect of self-monitoring of glucose on both diabetes specific emotional distress and glycaemic control in a large sample. In addition, due to a pre-stratification in oral treatments likely to cause hypoglycaemia or not, a possible interaction with type of treatment can be discovered. With the use of a theoretical model as a base for our hypothesis the evaluation of processes theoretically underlying the (in)effectiveness of our trial will be allowed as well. Therefore, this trial will make an important contribution to the evidence of self-monitoring in non-insulin requiring patients with T2DM.

Franciosi et al. [36] reported that a self-monitoring frequency of more than 1 measurement a day was related with the development of diabetes related distress in T2DM patients not using insulin. Unfortunately, mastering a new skill is coupled with practicing and thus a relatively high frequency. By offering participants in the intervention groups a training in self-monitoring, a control visit and a flowchart with instructions when to perform and how to interpret self-monitoring we believe that a 2 months period should be sufficient to familiarize with the self-monitoring skills considered necessary. In addition, development of diabetes-related distress caused by a high monitoring frequency is targeted by giving the participants the opportunity to independently adjust the prescribed self-monitoring frequency to one 'they feel comfortable with' starting two months after baseline.

As glycaemic control is an important issue in diabetes care most research regarding self-monitoring has focused on clinically relevant changes in HbA1c [16,37-40]. This trial primarily focuses on the effect of self-monitoring on diabetes specific distress and is additionally sufficiently powered to detect a clinically relevant decrease of 0.5% in HbA1c.

This trial will deliver important insights in the effects of self-monitoring of glucose in T2DM patients not using insulin on diabetes related distress and self-efficacy and the role of possible barriers and facilitators underlying its (in)effectiveness.

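### A data-driven choice between pooled and stratum-specific primary results raises type I error above the planned 0.025, and the trial is not sized to detect an SU interaction of 0.5 SD or less

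*Protocol article*

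**What the plan says.** Three sections of the protocol article bear on this point.

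- **Analyses:** "The subgroups SU and non-SU will be analysed separately for all outcome measures". The next sentence adds: "In case there is no effect modification by treatment the data of both subgroups will be pooled". The wording covers all outcomes, so it includes the two primaries, PAID and CIDS. No test, threshold or division of alpha between the strata is given.
- **Sample size:** alpha is corrected for the two primary outcomes only: "Using a bonferroni correction based on two primary hypotheses with α 0.025 and β 0.15". The requirement of 86 per group is then doubled because effects may differ between SU and non-SU patients. After an allowance for 15% drop-out, the total is 600.
- **Discussion:** because of the pre-stratification, "a possible interaction with type of treatment can be discovered". No size of interaction and no power are attached to this statement.

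**The concern.** The observed data settle which analysis answers the primary question. If the check finds no effect modification, one pooled test is done per comparison. If it finds some, two stratum tests are done, and either can be read as a positive result. A chance difference between strata is exactly the situation in which one stratum looks extreme, so the stratum tests are opened when they are most likely to be falsely positive. The Bonferroni correction covers two outcomes and does not reach this choice.

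The check is also weak. Doubling the sample gives each stratum the power originally planned for the whole trial. The contrast between two stratum effects has twice the variance of one stratum effect, and the trial was not sized for it. A check that finds nothing is therefore poor evidence that the effects are alike. If only one stratum benefits, the rule may pool and put forward a diluted average.

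**Working it through.** **Inputs from the Sample size section.** Alpha 0.025 per outcome and power 0.85. PAID: "In diabetes patients the standard deviation (SD) of PAID (scores transformed to 0–100) was 20 points", target difference 10 points. CIDS: "For type 1 diabetes patients the SD of CIDS (scores transformed to 0–100) was 12 points", target 6 points. Both targets are 0.5 SD. Drop-out is 15% and the total is 600, with three equal arms.

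**Assumptions.** Two-sided tests, equal SU and non-SU strata, interaction threshold 0.025 to 0.10, and no precision gained from baseline scores.

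**1. The plan's own figure.** n = 2(2.241 + 1.036)² / 0.5² = 85.95, so 86 per group for either outcome. This reproduces the stated 86; a one-sided test would give 72. Then 86 × 3 arms × 2 strata = 516. Dividing by 0.85 gives 608 and multiplying by 1.15 gives 594, both consistent with 600. Completers per arm and stratum: 600 × 0.85 / 6 = 85.

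**2. Type I error of the rule, one comparison and one outcome.** Under the null with equal strata, the pooled and interaction statistics are independent. Hence

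error = (1 − a) × 0.025 + a × P(either stratum significant | interaction significant),

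where a is the interaction threshold. The conditional probability comes from simulation with 6 million draws.

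| a | P(either stratum significant, given interaction) | Error | Ratio to 0.025 |
|---|---|---|---|
| 0.025 | 0.56 | 0.0385 | 1.54 |
| 0.05 | 0.42 | 0.0449 | 1.79 |
| 0.10 | 0.30 | 0.0520 | 2.08 |

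For example, at a = 0.05: 0.95 × 0.025 + 0.05 × 0.42 = 0.045. A 70:30 split changes little (0.0393, 0.0456 and 0.0521).

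**3. Where the excess comes from.** Testing both strata at 0.025 with no pooling step gives 1 − (1 − 0.025)² = 0.0494. Two uncorrected stratum tests thus account for most of it. Halving alpha within the strata but keeping the pre-test at 0.05 still leaves 0.037 (ratio 1.46), so the data-driven choice adds error of its own.

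**4. Power of the interaction test.** SE = √(4/85) = 0.217 SD. Power ≈ Φ(δ/0.217 − z).

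| Difference between strata | alpha 0.025 | alpha 0.05 | alpha 0.10 |
|---|---|---|---|
| 0.25 SD | 14% | 21% | 31% |
| 0.50 SD | 52.5% | 63.5% | 74.5% |
| 0.75 SD | 89% | 93% | 97% |

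For 85% power at alpha 0.05 the difference must be (1.960 + 1.036) × 0.217 = 0.65 SD. An interaction of 0.5 SD at alpha 0.025 and 85% power would need 172 per arm and stratum: 172 × 6 = 1,032 completers, or about 1,215 patients after dividing by 0.85. With a 70:30 split, power for 0.5 SD at alpha 0.05 falls to 56%.

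**5. Wrongful pooling.** If the effect is 0.5 SD in one stratum and zero in the other, the rule pools with probability one minus the power above: 47.5%, 36.5% and 25.5% at thresholds 0.025, 0.05 and 0.10. The pooled estimate then targets (0.5 + 0)/2 = 0.25 SD, or 5 PAID points.

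**6. Fixed pooled analysis.** With 170 completers per arm, SE = √(2/170) = 0.108 SD. Power for 0.5 SD at 0.025 is Φ(0.5/0.108 − 2.241) = 99.1%, with type I error 0.025.

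**The case against.** **The pooling sentence is not the main source of error.** This is correct. Separate testing without any pooling gives 0.049, slightly more than the 0.045 of the two-stage rule at threshold 0.05. Deleting the sentence and changing nothing else would gain nothing. One may also hold that two strata sized separately are two questions, each tested at its own 2.5%. That is defensible if declared in advance; the article instead lets the data decide whether there are one or two questions.

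**The threshold is unknown and may be set in the full protocol or analysis plan.** This also stands. A reader might infer that type I error is nearly doubled. The article does not support one such figure: the ratio is about 1.5 to 2.1 at nominal 0.025 over the thresholds examined. With a joint two-degree-of-freedom test over three arms it is 1.55 to 1.81 (thresholds 0.05 and 0.10). Naming a threshold would define the pre-test but not remove it.

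**Power could be better than shown.** The primary outcomes are changes from baseline. If baseline is a covariate and its correlation with follow-up is 0.5 to 0.7 (an assumption), the SE shrinks by √(1 − r²). Power for 0.5 SD at alpha 0.05 then becomes about 76% to 90%. Unequal strata work the other way. The figures above are therefore conditional on their assumptions.

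**The Discussion names no size of interaction.** A reader might infer that its claim is false. That goes too far, since a 0.65 SD interaction has 85% power and a 0.75 SD interaction 93% at alpha 0.05.

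**A pooled primary also dilutes a one-stratum effect.** True, and it does so every time. This is why the interaction and stratum estimates must always accompany it.

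**Conclusion.** The point holds in limited form. The article affirmatively states a rule that lets an effect-modification check choose the form of the primary result, with alpha not shared between strata. Followed as written, it gives a type I error per comparison of about 0.038 to 0.052 instead of 0.025. This rests on equal strata, 85 completers per arm and stratum, two-sided tests and an interaction threshold between 0.025 and 0.10. Uncorrected testing of two strata is the larger cause and the pre-test a smaller, separate one.

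On the design inputs, with no gain from baseline adjustment, the trial is not sized for an interaction of 0.5 SD or less. The unpooled route itself is not underpowered: each stratum has about 85% power for 0.5 SD if the strata are equal, although no quota ensures that.

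**What to change.** - **Analyses:** replace the conditional pooling sentence with a primary analysis fixed in advance, namely the pooled comparison of each intervention arm with usual care, adjusted for SU stratum, at alpha 0.025 per outcome. Report the arm-by-SU interaction with its confidence interval and both stratum estimates as secondary results, whatever the interaction test shows.
- **Alternative:** if the sponsor wants stratum-specific primaries, fix them in advance, split alpha over the strata and drop the pre-test. At 0.0125 per stratum, power for 0.5 SD with 85 per arm is Φ(0.5/√(2/85) − 2.498) = Φ(0.76), about 78%, instead of about 85%.
- **Discussion:** say that the trial is not sized to detect an interaction of 0.5 SD or less, and state the assumptions (strata of equal size, 85 completers per arm and stratum, no baseline adjustment).

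**Cost.** No new patients or data. It is more than a wording change, however: stratum results, for which the sample was doubled, become secondary, and the statement about interaction becomes less favourable.

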### Randomization

For intervention allocation a randomization list is drawn up using a computerized randomization computer program (Random Allocation Software version 1.0.0). As different effects may be expected of prescribed drug treatments that are likely to cause hypoglycaemia, for example sulfylureas or glinides (SU), randomization will be pre-stratified by treatment (using SU or not (Non-SU)). A research-manager, who is not involved in the patients care, allocates the patient to one of the 3 groups by using the randomization list. Intervention allocation will be concealed for the principal investigator who is responsible for the data analyses. Participants may withdraw from the study at their own request and without providing reasons. Date of withdrawal will be recorded and effort will be made to contact participants lost to follow up. Only participants withdrawn prior to randomization will be replaced.

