### Measurements

Outcome measures are obtained at baseline, 4 and 12 months. These are collected by self-administered questionnaires, blood sampling and anthropometry. Diabetes specific distress is assessed by the Problem Areas In Diabetes scale (PAID) [24,25] and self-efficacy by the Confidence In Diabetes Self-care questionnaire (CIDS) [26] adjusted for T2DM. Patient treatment satisfaction is assessed by the Diabetes Treatment Satisfaction Questionnaire (DTSQ) [27], physical activity is assessed by the short International Physical Activity Questionnaire (IPAQ-7) [28], health status and cost utility are assessed with the Euroqol-5D [29-31]. Status of depression is assessed at baseline and at 12 months using the Patient Health Questionnaire-9 (PHQ-9) [32], Demographic variables on age, gender, diabetes duration, marital status and level of education are assessed at baseline by means of a self-administered questionnaire. Glycaemic control is measured by HbA1c-level. Furthermore, BMI and blood-pressure are measured. Participants are asked to register occurrence of hypoglycaemia in care-diaries. Costs of direct health care and indirect non-healthcare will be inventoried in cost-diaries and recorded in 3-monthly intervals. Table 1 summarizes the measures and their timing.

**Table 1 T1:** Study measures

**Measures**	**Baseline**	**2 months**	**3 months**	**4 months**	**6 months**	**9 months**	**12 months**

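### Baseline adjustment depends on an undefined observed imbalance, so the primary model is not fixed and the baseline PAID or CIDS score is not assured a place in it

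*Protocol article*

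**What the plan says.** The Analyses section sets the rule for covariates: "If there are any relevant differences in baseline measurements between the 3 arms, we will adjust the outcomes for these factors". A parenthesis then lists seven factors: age, gender, ethnicity, depression, duration of diabetes, marital status and education. Baseline PAID, baseline CIDS and SU use are not among them. The model is described only in general terms: "Linear and logistic regression will be used to determine the effect of the intervention on each of the outcome measurements".

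Four other parts of the article bear on this.

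- The objectives define both primary outcomes as changes, and Table 1 has PAID and CIDS measured at baseline.
- The Randomization section says that "randomization will be pre-stratified by treatment (using SU or not (Non-SU" is the stratification. The Analyses section analyses the two SU groups separately and pools them if treatment does not modify the effect. It states no SU term for the pooled model.
- The Measurements section says "Demographic variables on age, gender, diabetes duration, marital status and level of education are assessed at baseline". Ethnicity is not in that list.
- The Sample size section uses the SD of a single score: "the standard deviation (SD) of PAID (scores transformed to 0–100) was 20 points".

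**The concern.** In a randomised trial, baseline differences between arms arise by chance. A rule that adjusts only when such a difference is judged relevant leaves two things open until the data are seen: whether to adjust, and for what. Without a definition of relevant, two analysts could apply the rule correctly and report different primary estimates.

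The rule also selects covariates on the wrong criterion. A covariate improves precision because it predicts the outcome, not because it happens to be unbalanced. The baseline value of the same questionnaire is usually the best predictor available, and under this rule it enters the model only if it looks unbalanced, if at all.

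At stake are the precision of the SU and non-SU analyses, for which the sample was doubled, and a primary model that is settled before the arms are compared.

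**Working it through.** **Inputs from the Sample size section.** "Using a bonferroni correction based on two primary hypotheses with α 0.025 and β 0.15, a sample size of 86 per group is needed" to detect 10 points on PAID with SD 20. CIDS uses 6 points with SD 12, which is the same standardised effect of 0.5, so the results below apply to both scores. Assumed dropout is 15%.

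**Assumptions.** The article gives no correlation r between baseline and follow-up scores; 0.4 to 0.7 is assumed. The SD is taken as equal at both times. SU and non-SU are taken as equal in size.

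**The plan's own figure.** Two-sided normal approximation:

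n = 2 × (2.2414 + 1.0364)² × (20/10)² = 85.95, rounded up to 86.

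This reproduces the article. Then 86 × 3 arms × 2 strata = 516. Dropout gives 516 × 1.15 = 594 or 516/0.85 = 608. The stated 600 is close to both.

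**Variance of each analysis, as a multiple of SD².**

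- Follow-up score only: 1
- Change score, unadjusted: 2(1 − r)
- ANCOVA on the baseline score: 1 − r²

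ANCOVA against change scores: (1 − r²)/[2(1 − r)] = (1 + r)/2, a reduction of (1 − r)/2. That is 30% at r = 0.4 and 15% at r = 0.7. ANCOVA against follow-up only: a reduction of r², that is 16% at r = 0.4 and 49% at r = 0.7.

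**Power in one SU stratum, 86 per group.** Power = Φ(10/SD* × √43 − 2.2414), where SD* is 20 times the square root of the variance multiple.

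| r | SD*, change | Power, change | SD*, ANCOVA | Power, ANCOVA |
|---|---|---|---|---|
| 0.4 | 21.9 | 77% | 18.3 | 91% |
| 0.5 | 20.0 | 85% | 17.3 | 94% |
| 0.6 | 17.9 | 92% | 16.0 | 97% |
| 0.7 | 15.5 | 98% | 14.3 | 99% |

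A follow-up-only comparison has 85% power at every r.

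**Pooled strata.** With 200 × 0.85 = 170 evaluable per arm, change-score power is 97.5% at r = 0.4 and 99.1% at r = 0.5. ANCOVA gives 99.7% and 99.9%. Even at r = 0.3 the figures are 95.1% and 99.5%.

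**How often the trigger would fire by chance.** If relevant meant p < 0.05 on seven independent factors (an assumption), at least one would qualify in 1 − 0.95⁷ = 30% of trials.

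**Type I error.** In 60,000 simulated null trials per correlation, with 170 per arm, the follow-up score was adjusted for baseline only when baseline differed at p < 0.05. At nominal 0.025 the rejection rate was 0.020 at r = 0.5 and 0.016 at r = 0.7. Fixed ANCOVA gave 0.025 at both.

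**Leaving SU out of the pooled model.** With equal strata whose outcome means differ by d SD, the standard error is inflated by √(1 + d²/4) − 1. That is 0.1% at d = 0.1 and 3.1% at d = 0.5 (d assumed).

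**The case against.** The strongest reply is that the article does not exclude the baseline score. PAID and CIDS are themselves baseline measurements, so the trigger could cover them. The listed factors may be only examples: the Economic analyses section uses *i.e.* where examples are evidently meant. The outcomes are changes, so baseline already enters. Exact model terms are commonly left to a fuller document. This stands against any claim that baseline is ignored. It does not rescue the rule. If the list is illustrative, the baseline score still enters only when it looks unbalanced; if the list is closed, it never enters as a covariate. The rule is also stated text, so it is not something merely left to an analysis plan.

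A reader might infer that the SU stratum is ignored. It is not: the two groups are analysed separately, and only the pooled model lacks a stated term, at a cost of about 0% to 3% of the standard error.

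A reader might also infer from the 77% figure that the trial is underpowered. That figure applies to one stratum at the lowest correlation in the assumed range. From r = 0.5 upward the change score meets the planned 85%, and the pooled analysis has ample power throughout.

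Finally, a reader might take the regression wording as a commitment to drop participants with missing visits. The article does not say so.

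**Conclusion.** The point holds as a matter of precision and pre-specification. The stated rule lets observed imbalance, judged by an undefined standard, decide the primary model, and it does not assure the baseline score a place there. ANCOVA was more precise at every correlation tried. Within one SU stratum the gain in power over change scores is about 14 percentage points at r = 0.4, 9 at r = 0.5 and 1 at r = 0.7. These figures rest on a correlation that the article does not give, and on equal SDs at baseline and follow-up.

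It would be tempting to conclude that the rule makes the nominal intervals anti-conservative or inflates type I error. The check does not support that: the triggered rule, as simulated, was conservative. The simulation covers one mechanical trigger on the baseline score and does not cover free choice by an analyst, which is why discretion remains a cost. The sample size is not in error on this account, since 86 per group reproduces and claims no gain from adjustment.

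The mismatch over ethnicity is small but real within the article's own text.

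**What to change.** Replace the imbalance rule in the Analyses section with a fixed model.

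1. For each primary outcome, within each SU stratum, fit a linear model of the follow-up score on arm and the baseline value of the same score, whatever the observed balance. Using change as the response, with baseline in the model, gives the same arm effect, so the outcome can still be described as change.
2. In the pooled model, add SU stratum as randomised.
3. Name any further covariates in advance and include them regardless of observed balance.
4. Reconcile ethnicity: either add it to the baseline variables collected or remove it from the adjustment list.

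The cost is a change of wording. Baseline PAID, baseline CIDS and SU status are already recorded, so no participants or visits are added. Only ethnicity, if kept, might need one more baseline item. The rule for pooling the SU groups is also data-dependent; this change leaves it as it stands.

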### IN CONTROL Objectives

The aim of the study is to assess the effects of SMBG and SMUG in patients with type 2 diabetes who are not using insulin compared to usual care. Primary outcome measures are changes in diabetes specific emotional distress and self-efficacy. Secondary outcomes are changes in glycaemic control, patient treatment satisfaction, physical activity, health status, status of depression, occurrence of hypoglycaemia, cost-effectiveness and cost-utility. As part of a process evaluation changes in illness perceptions, perceived severity and social support are determined as well.

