### Study population

In total 600 consenting participants will be recruited. Patients are considered eligible if they are diagnosed with T2DM and meet the following criteria:

❑ known disease duration of over 1 year

❑ recent HbA1c ≥ 7.0%

❑ treated with diet and/or oral hypoglycaemic agents

❑ do not require insulin at inclusion

❑ aged between 45 and 75 years

❑ used SMBG or SMUG less than 3 times in the previous year

Participants will be randomly assigned to one of the following 3 groups (figure 1):

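### The named subgroup factors leave out baseline PAID and CIDS, so no named analysis separates no effect on distress or self-efficacy from little room to improve

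*Protocol article*

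**What the plan says.** The objectives state: "Primary outcome measures are changes in diabetes specific emotional distress and self-efficacy". Under Measurements, "Diabetes specific distress is assessed by the Problem Areas In Diabetes scale (PAID") and self-efficacy by the CIDS. The timing rule is "Outcome measures are obtained at baseline, 4 and 12 months", and Table 1 shows both instruments at baseline.

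The six entry criteria under Study population include "recent HbA1c ≥ 7.0"% and "used SMBG or SMUG less than 3 times in the previous year". None concerns distress or self-efficacy.

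The Sample size section gives the spread of the PAID but no expected mean: "In diabetes patients the standard deviation (SD) of PAID (scores transformed to 0–100) was 20 points". From this, "a sample size of 86 per group is needed to find a difference of 10 points (0.5 SD"). SU users and non-users are to be analysed separately, and pooled if treatment does not modify the effect.

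To find out which patients gain most, the Analyses section estimates effects in "sub-groups defined by duration of diabetes, socio-economic status, perceived social support and perceived severity of diabetes, glycaemic control and self-monitoring frequency". It also announces moderator and mediator analyses for the process evaluation without naming variables. The process-evaluation section describes its measures as subscales of the IPQ-R and the MDQ.

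**The concern.** The article commits to a specific list of modifiers for a specific purpose. The list includes glycaemic control, the variable used for entry. It omits the variable that limits how far a patient can improve on each primary outcome. A patient who starts below 10 on a 0–100 distress scale cannot fall by 10 points, and a patient who is already confident has little room on the CIDS.

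Two readings of the PAID result depend on this. If many participants start with little distress, the mean difference shrinks even when monitoring helps everyone who has room to improve. If monitoring relieves distressed patients and burdens others, the two effects can offset each other in the average. The protocol takes the second possibility seriously: its background reports qualitative evidence of negative impact, its Discussion cites a study linking frequent monitoring to distress, and it lets participants reduce their monitoring frequency after two months. None of the named subgroups tests either pattern directly. An analysis by baseline distress chosen after a disappointing result would carry much less weight than one fixed beforehand.

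**Working it through.** **1. The plan's own figure.** Inputs from the Sample size section: difference 10, SD 20, α 0.025 (taken as two-sided), power 0.85.

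n = 2 × [SD × (z₀.₉₈₇₅ + z₀.₈₅) / difference]² = 2 × [20 × (2.2414 + 1.0364) / 10]² = 85.95, so 86 per group. This matches.

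Two strata and three arms give 86 × 2 × 3 = 516. Dropout of 15% gives 516 / 0.85 = 608 (rounded up), or 516 × 1.15 = 594 (rounded up). The stated 600 lies between them. The sample-size figures are not in dispute.

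**2. Completers.** 200 × 0.85 = 170 per arm pooled. If the two strata are of equal size (an assumption), 85 per arm per stratum. Without any floor, power is 85% and 99%.

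**3. Floor model (assumption).** Scores follow a beta distribution on 0–100 with SD 20 and mean m, and usual care does not change. Every monitored patient falls by 10 points, or to 0 if the score is below 10.

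- Shape: μ = m/100, k = μ(1 − μ)/0.20² − 1, a = μk, b = (1 − μ)k.
- Attainable mean fall: d = E[min(score, 10)].
- s = root mean square of the SDs in the two arms.
- Power = Φ(d / (s√(2/n)) − 2.2414).

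Example for m = 20: k = 0.16/0.04 − 1 = 3, a = 0.6, b = 2.4; d = 7.26, s = 18.9. With n = 85 the standard error is 18.9 × √(2/85) = 2.90, the ratio is 2.50, and power is Φ(0.26) = 60%. With n = 170 the ratio is 3.54, and power is 90%.

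| Assumed mean PAID (SD 20) | Share below 10 | Attainable mean fall | Power, one stratum (85 per arm) | Power, pooled (170 per arm) |
|---|---|---|---|---|
| 15 | 59% | 5.5 | 37% | 68% |
| 20 | 43% | 7.3 | 60% | 90% |
| 25 | 29% | 8.5 | 73% | 97% |
| 30 | 18% | 9.2 | 80% | 98% |
| 40 | 5% | 9.8 | 84% | 99% |

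**4. Sensitivity to the SD.** With mean 15 and SD 15, half the patients score below 10 and the attainable fall is 6.9. Power is still 84% per stratum and 99% pooled, because the smaller spread compensates.

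**5. What an interaction analysis could detect.** As a rough guide, let a share p of patients have a 10-point effect and the rest none, with SD 20, 170 per arm and a two-sided interaction test at 0.05. The standard error is 20 × √[2/(170p) + 2/(170(1 − p))].

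- p = 0.3: SE 4.73, ratio 2.11, power Φ(2.11 − 1.96) = 56%.
- p = 0.5: SE 4.34, ratio 2.30, power Φ(2.30 − 1.96) = 63%.

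No similar table is possible for the CIDS ceiling without a further assumption. The article gives an SD of 12 from type 1 patients and no mean.

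**The case against.** A reader might infer that a null result on distress could never be told apart from a floor effect. The documents do not support that. PAID and CIDS are collected at baseline in all arms, so the baseline distribution, the share near zero and an arm-by-baseline interaction can all be obtained from planned data. What is absent is a named, pre-specified analysis.

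A reader might also infer that enrolling on HbA1c rather than distress is a design error, or that the trial is underpowered. Neither follows. The stated aim concerns non-insulin patients in general, which is a legitimate population. The 10-point target is a difference between groups, not a fall required of each patient, and it could arise partly from worsening under usual care. A floor is assumed, not documented. In the model above, pooled power stays at 90% or more unless the mean is below 20.

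Three further objections have some force. First, modelling detail commonly belongs in an analysis plan that is not shown. That holds for the form of the terms. But the article itself names the factors for this question, and the unnamed moderators are tied to a process evaluation with other measures. Second, perceived severity and monitoring frequency are on the list and bear on distress and burden. They are related to baseline distress but do not measure room to improve on the PAID. Third, an interaction test has limited power, so a null interaction would not settle the matter. That favours a continuous term with estimates and intervals over a significance test in a split sample.

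**Conclusion.** The point holds as a gap in the pre-specified list, not as a flaw in the primary comparison. The article asks who gains most and omits the baseline level of both primary outcomes.

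The consequence depends on a baseline PAID mean that the documents do not give. The loss of power is small if the mean is 30 or more and the strata are pooled. It becomes serious at low means, chiefly within an SU stratum: 60% at a mean of 20 and 37% at a mean of 15, against 85% planned. These figures rest on SD 20, a beta shape, equal strata, 15% dropout and a uniform 10-point effect cut off at zero. A smaller SD would weaken or remove the loss. The CIDS argument is the same in kind but is not quantified.

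This is a worthwhile, low-cost improvement to interpretation. It does not show that a null result is likely.

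**What to change.** Leave eligibility and sample size unchanged. In the Analyses section:

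- Add baseline PAID for the PAID outcome, and baseline CIDS for the CIDS outcome, as covariates and as pre-specified continuous arm-by-baseline interaction terms.
- Report the estimated effect of each intervention against usual care, with its confidence interval, at low, median and high baseline scores. Define these levels in advance.
- Label the analysis exploratory and state that a non-significant interaction does not exclude a floor.

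The data are already planned, so there is no extra visit, instrument or patient. The cost is one more exploratory modifier per primary outcome, with limited power.
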